## Method

### Setting and participants

The intervention is designed for implementationwithin mainstream high school counseling settings serving adolescents aged 14–18. This ecological frame is intentional. As a feasibility study, the sample size is determined by the need to evaluate implementation applicability and estimation precision rather than statistical power for clinical efficacy. A target sample of 40–60 students from routine school caseloads, is sufficient to yield narrow confidence intervals (CIs) for recruitment/retention/compliance and to visualize heterogeneous individual-level micro-trajectories within an authentic delivery context. Feasibility will be evaluated against four pre-specified operational thresholds: (a) a recruitment rate ≥ 70% of eligible students; (b) a retention rate of ≥ 80% (defined as completing both pre- and post-intervention trait measures); (c) a median EMA compliance of ≥ 60% for daily prompts (1–7 Likert scale) across Weeks 1–8; (d) an intervention fidelity of ≥ 75% (defined as weeks where all three checklist items are met). These thresholds were derived from established benchmarks in the feasibility and pilot trial literature (Billingham et al., 2013; Eldridge et al., 2016). The 70% recruitment and 80% retention rates are widely adopted as minimum indicators of a viable study pipeline for a subsequent full-scale trial. The 60% EMA compliance threshold reflects the empirically observed lower bound of acceptable ecological momentary data completeness in adolescent digital health studies (Shiffman et al., 2008); compliance below this level produces phase lengths insufficient for reliable Tau-U estimation. The 75% fidelity threshold is grounded in the intervention science literature’s recommendation that at least three-quarters of protocol sessions be delivered as specified before efficacy conclusions can be considered (Bellg et al., 2004). Together, these benchmarks ensure that a positive feasibility verdict is substantively meaningful rather than nominally so.

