Quantitatively, the design combines a within-subject trait-level pre–post comparison with an embedded single-case AB probe. The sequence consists of a pre-intervention baseline (Phase A; Weeks −2 and −1) and an active intervention period (Phase B; Weeks 1–8). The two-week baseline was adopted. A minimum of 10 data points in Phase A provides a more stable trend estimate for Tau-U baseline correction and more clearly distinguishes pre-existing directional drift from intervention-related change. Throughout Phase B, state-level EMA micro-ratings (1–7 Likert scales) index continuously index momentary regulation states. Trait-level self-regulation and social connectedness are measured at pre- and post-intervention timepoints via the within-subject standardized mean difference (Cohen’s *d*). To rigorously capture the dynamics of the state-level micro-trajectories, data will be evaluated using Tau-U, a robust, best-practice non-overlap effect size optimized for AB sequences in single-case experimental design (SCED) methodology.

The qualitative strand consists of (a) weekly counselor fidelity logs and (b) brief, one-sentence reflective student notes. These materials are not narrative interviews; rather, they serve as real-time process-evidence. Therefore, the analytic objective is not to achieve thematic saturation, but to execute mechanism-alignment detection. Reflexive thematic analysis will be used to identify and verify whether developmental practice indicators outlined in Table 1 occurred within a real-world educational environment.

All reflective notes remain accessible to the counselor to preserve the core ethical principle of human relational containment. The AI system does not store raw text beyond the generation of summary logs. Data retention adheres strictly minimal-retention feasibility norms; export functions are disabled. No participant data or conversational data is used for model training or model improvement. Furthermore, no algorithmic action is permitted without the possibility of immediate human override; should emotional dysregulation signals emerge, counselors escalate the case in accordance with established institutional safeguarding protocols. In this design, the AI is never the locus of clinical decision; rather, it is the engine for prompt density. Human counselors retain absolute safeguarding authority and interpretive control.

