#### Missing data handling

Missing data for the trait outcomes (BSCS, SSBS), analyses will be managed via pairwise availability with sensitivity checks using last-observation-carried-forward for descriptive ranges. For the state-levelEMA data, missing days will simply be omitted because Tau-U inherently tolerates unequal phase lengths and missing data points within time-series sequences. To rigorously assess the effect of intervention dosage, per-participant compliance (percentage of EMA prompts answered) will be reported and descriptive contrasts comparing high- compliance (≥ 60%) versus low- compliance (< 60%) will be conducted.

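### The only analysis relating compliance to outcome is a two-group split at 60%, which costs precision and, if applied to Tau-U, makes the low group the students whose estimates the protocol calls unreliable

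*Protocol article*

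**What the plan says.** The Missing data handling section of the protocol article states the aim and the exposure variable in one sentence: "To rigorously assess the effect of intervention dosage, per-participant compliance (percentage of EMA prompts answered) will be reported". The same sentence continues that "descriptive contrasts comparing high- compliance (≥ 60%) versus low- compliance (< 60%) will be conducted". It names no outcome for the contrast, and no other analysis in the article relates compliance to outcome.

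The 60% figure comes from Setting and participants, where it is a feasibility criterion: "a median EMA compliance of ≥ 60% for daily prompts (1–7 Likert scale) across Weeks 1–8". It is defended there as a lower bound of acceptable completeness for EMA data, with the added reason that "compliance below this level produces phase lengths insufficient for reliable Tau-U estimation". The sample size is given in the same section: "A target sample of 40–60 students from routine school caseloads".

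For the EMA series, Missing data handling says that "missing days will simply be omitted because Tau-U inherently tolerates unequal phase lengths and missing data points within time-series sequences". Students below 60% therefore keep a Tau-U value. The Data analysis strategy plans 95% confidence intervals for the trait outcomes and says significance testing is not required.

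**The concern.** Compliance is recorded for each student as a percentage. The contrast reduces it to two groups, so 59% and 61% count as different while 61% and 100% count as the same. The stated reason for 60% concerns whether there are enough data points. Nothing in the article suggests that response changes at that level, so it has no standing as a dose cut.

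Two things are at stake. First, with 40–60 students, the split gives a less precise description of how outcome varies with compliance than the same data allow. Precision worsens as the low group shrinks, which is what happens as compliance improves. Second, if the outcome contrasted is Tau-U, one whole side of the comparison consists of students whose estimates Setting and participants treats as unreliable, while Missing data handling treats the gaps as harmless.

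**Working it through.** The article gives no precision or power figure for this contrast, so there is nothing of its own to reproduce. The check measures what the split costs.

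**Inputs from the article:** n = 40–60; cut at 60%; feasibility target of a median of at least 60%, so about half the students or fewer fall below the cut if the target is met.

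**Assumptions, not in the article:** the shape of the compliance distribution, a linear relation with outcome, and the share p of students below 60%.

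**1. Information kept by the split.** Relative to a linear analysis of the percentage, this is the squared correlation between compliance and the high/low indicator. For normal compliance it equals φ(z_p)² / [p(1−p)].

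- p = 0.50: 0.637 kept, 36% lost. Equivalent to about 25 of 40 or 38 of 60 students.
- p = 0.25: 0.539 kept, 46% lost.
- p = 0.15: 0.426 kept, 57% lost. Equivalent to about 17 of 40 or 26 of 60 students.
- p = 0.10: 0.342 kept, 66% lost.

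In interval width, 1/√0.637 = 1.25 and 1/√0.426 = 1.53. The split gives intervals about 25% wider at an even split and about 53% wider with 15% low.

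**2. Other shapes.** Compliance is bounded, so the same quantity was computed for Beta distributions cut at 0.60.

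- Beta(3,2), 48% low: 31% lost.
- Beta(5,2), 23% low: 38% lost.
- Beta(6,2), 16% low: 45% lost.
- Beta(8,2), 7% low: 61% lost.
- U-shaped forms: 21–23% lost.

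A fair range over shapes and shares is roughly 20–65%.

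**3. Precision of the high–low difference.** The half-width in outcome SD units is 1.96 × √(1/n₁ + 1/n₂).

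- n = 40, 20 v 20: 0.62. n = 60, 30 v 30: 0.51.
- n = 40, 6 v 34: 0.87. n = 60, 9 v 51: 0.71.

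**4. Tau-U.** The null standard error of the non-overlap Tau, before trend correction, is √[(a+b+1)/(3ab)] for a baseline and b intervention points. The article does not say whether prompts run on calendar or school days. With equal compliance in both phases:

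- Calendar days (14 and 56 prompts): 0.17 at full compliance, 0.23 at 60% (8 and 34), 0.27 at 40% (6 and 22).
- School days (10 and 40 prompts): 0.21, 0.27 (6 and 24) and 0.33 (4 and 16).

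Precision falls gradually, with no break at 60%. The high group is not assured good baselines either. Research design relies on this: "A minimum of 10 data points in Phase A provides a more stable trend estimate for Tau-U baseline correction". Sixty per cent of Phase A is 0.6 × 14 = 8.4 or 0.6 × 10 = 6 points, both below 10.

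**The case against.** The strongest reply is that the contrast is descriptive. The article plans no test, disclaims causal and efficacy conclusions, and says in the same sentence that "per-participant compliance (percentage of EMA prompts answered) will be reported". The percentages are therefore kept, and the cut is pre-specified. Because the sentence sits under missing data, the split can be read as a check on whether results depend on students with sparse series.

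Much of this stands. The continuous data are not lost; the loss concerns only the two-group contrast. But reporting each percentage does not relate it to outcome, a descriptive estimate still needs precision, and the article itself gives the purpose as a rigorous assessment of dosage.

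Some stronger readings are tempting but unsupported:

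- **That a real gradient would probably be reported as no dose relation.** No test is planned. In illustrative simulations with a compliance–outcome correlation of 0.3–0.5, a two-sided 5% test on an even split has 32% power at n = 40 and correlation 0.3, but 91% at n = 60 and correlation 0.5. In the weakest of these cases (n = 40, correlation 0.3), the continuous analysis itself reaches only 48%.
- **That a later randomised trial would set its dose from this contrast.** The article does not say so.
- **That the Tau-U conflict undermines the contrast for every outcome.** The outcome is not named, and BSCS and SSBS change do not depend on the length of the EMA series.

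**Conclusion.** The point holds as a cheap improvement to an exploratory analysis. The 60% cut has no dose rationale in the article, and splitting there is less precise than using the percentage already computed. The loss is about 36–57% of the information under normal compliance, a linear relation and 15–50% of students below the cut, and roughly 20–65% over other plausible shapes and shares. The article states none of these conditions, so 36% is not a floor and 57% is not a ceiling.

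For Tau-U, the two sections pull against each other, and the contrast would set apart exactly the students whose estimates are called unreliable. This applies only if Tau-U is the outcome contrasted.

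The stated aim also promises too much whichever scale is used. Answering EMA prompts is measurement behaviour, whereas the intervention consists of nudges, coaching dialogues and mini-sessions, and nudge opening is logged separately in the fidelity checklist. The feasibility verdict against the four thresholds does not depend on this contrast.

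**What to change.** Replace the contrast in Missing data handling with:

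> The relation of per-participant EMA compliance (percentage, kept continuous) to BSCS change, SSBS change and Tau-U will be described with a scatterplot, a Spearman correlation and a linear slope per 10 percentage points, each estimate with a 95% CI. The ≥60%/<60% split is tabulated for feasibility reporting only.

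Describe the result as an association with EMA compliance, and drop the claim to a rigorous assessment of dosage. Flag Tau-U values from students below 60%, in line with Setting and participants. Weighting Tau-U by its inverse variance is optional: the weights depend on series length, and so on compliance itself, and would down-weight the low end of the range.

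The cost is a short change of text. No new data are needed. A slope and plot are slightly less simple to present than two group means, and the slope assumes linearity, which the scatterplot and Spearman estimate check.

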### Practical contribution

The primary practical contribution of this feasibility protocol is not to establish causal efficacy, but in solving a foundational translational problem in implementation science. Complex socioemotional interventions often fail in fully powered randomized controlled trials (RCTs) not because the underlying developmental theory is flawed, but because the delivery mechanisms are incompatible with real-world school environments. By successfully mapping relational developmental systems theory onto an actionable digital delivery system, this protocol provides a rigorously specified protocol and open-source methodological blueprint that future researchers can adopt as an intervention for fully powered RCTs. It forms links between abstract theoretical goals and concrete, ecological implementation. Ultimately, this model functions as a transferable developmental scaffold specifying developmental arc, AI-augmented dosage logic, human-in-the-loop safety structure, and measurement architecture necessary for rigorous clinical replication. By establishing clear operational compliance targets, setting ethical boundary conditions for artificial intelligence, and illustrating how to synthesize quantitative time-series metrics with qualitative mechanism evidence, this protocol significantly reduces the friction for future outcome research. Researchers and clinicians can adapt it across different adolescent populations and diverse socioeconomic and cultural settings, alternative developmental targets, or varied educational environments, thereby accelerating the field’s progression toward rigorous, large-scale efficacy testing of AI-supported and AI-augmented developmental interventions.

### Limitations

Given its architecture as a feasibility design, this study cannot causally attribute observed changes to the intervention, nor does it make any statistical inference regarding comparative superiority or clinical efficacy. Any observed trait- or state-level shifts may be confounded by normative developmental maturation, placebo engagement, social desirability, technological novelty effects, or seasonal artifacts of the school calendar. Furthermore, the fidelity documentation is strictly designed to assess the mere presence of mechanism enactment, not the qualitative depth or mastery of the skill. Consequently, no estimates of generalizability are proposed or assumed.

In addition to the design-level constraints noted above, several AI-specific risks warrant explicit acknowledgment, as these are now priority concerns in educational AI literature. First, LLMs are susceptible to hallucination, meaning the model may occasionally generate factually inaccurate or contextually inappropriate responses. Although the system’s rule-based prompt architecture constrains output to MI-style reflective templates and reduces this risk, it cannot be entirely eliminated. Counselors are therefore instructed to review flagged interactions and to treat any factually dubious AI output as a fidelity concern requiring immediate intervention. Second, algorithmic bias may be present in the underlying model’s training data. Students from minority cultural, linguistic, or socioeconomic backgrounds may encounter prompts that implicitly reflect dominant-cultural norms or fail to resonate within their relational context. The pre-deployment audit described in the AI System Specification section includes sensitivity review by raters with diverse cultural backgrounds; however, residual bias cannot be fully excluded and should be documented during implementation. Third, emotional dependence on the AI system is a theoretically plausible risk, particularly for adolescents experiencing social isolation or acute relational distress. The protocol mitigates this risk structurally by maintaining the weekly counselor mini session as a non-negotiable relational anchor and by ensuring the AI’s role is framed to students as a practice tool rather than a relational agent. Counselors are trained to monitor engagement patterns and to intervene if a student’s interaction frequency suggests substitution of AI contact for peer or counselor relationships. These risks do not invalidate the feasibility rationale of the study, but they underscore the necessity of maintaining robust human oversight throughout the protocol.

### Future directions

Future research should move beyond evaluating whether AI-augmented interventions “work” and begin examining how developmental mechanisms unfold across ecological time. In PYD-oriented intervention science, this shift may allow researchers to conceptualize development not as a static pre–post outcome, but as a dynamic sequence of micro-enactments occurring across everyday contexts. AI-supported EMA systems may therefore contribute to a broader methodological transition from episodic intervention models toward continuous developmental process monitoring.

Within PYD literature specifically, future studies may explore whether AI-enhanced delivery systems can strengthen underexamined developmental pathways such as resilience transfer, identity coherence, future orientation, and culturally contextualized belonging. The flexibility of AI-supported micro-interactions may also enable more adaptive and personalized developmental scaffolding, including culturally responsive framing, language-sensitive prompts, and differential pacing based on student engagement patterns. Such possibilities are particularly relevant for school counseling systems that operate under high relational demand and limited institutional capacity.

Future work should additionally investigate whether AI-assisted interventions can support relational continuity rather than merely increasing digital interaction frequency. Rather than conceptualizing AI as a substitute for counselor expertise, subsequent research may examine how AI can preserve counselor emotional bandwidth by redistributing repetitive micro-support tasks while maintaining human interpretation, ethical judgment, and developmental attunement as central features of care.

At the methodological level, future studies may integrate passive sensing data, adaptive intervention sequencing, and reinforcement-learning informed prompt timing to examine whether developmental support can become increasingly context-responsive without compromising ethical safeguards. However, these advances should be approached cautiously. Future AI-based psychological interventions must continue prioritizing transparency, human oversight, bias mitigation, and youth protection frameworks, particularly in school-based contexts involving minors. Ultimately, the long-term contribution of AI in PYD research may not lie in replacing human developmental relationships, but in expanding the temporal and ecological reach of those relationships in ways that were previously impractical within conventional counseling delivery systems.

## Conclusion

This paper presented a study protocol and outcome research design for an AI-augmented PYD intervention intended for school counseling settings. Rather than positioning artificial intelligence as a replacement for human counseling relationships, the proposed model conceptualizes AI as a structured developmental support mechanism capable of extending the frequency and ecological reach of reflective micro-interactions within adolescents’ daily lives. By integrating PYD theory, mixed-method outcome research, EMA, and SCED methodology, the paper offers a transparent and replication-ready framework for future feasibility and controlled intervention studies. More broadly, the proposed design contributes to emerging discussions regarding how psychological science can responsibly integrate AI into educational and counseling practice without diminishing the importance of human judgment, relational attunement, and ethical oversight. As schools continue to face increasing developmental demands alongside limited counseling capacity, AI-supported intervention architectures may offer one pathway for expanding developmental opportunities while preserving the counselor–student relationship as the central foundation of care.

## Appendix

### Appendix A: sample micro-nudge scripts (week examples)

Week 1 – Awareness: “Notice one emotion you felt today. Name it. That alone is a skill.”

Week 3 – Regulation Moves: “When tension rises, take one slower breath than usual. Small slows count.”

Week 5 – Prosocial Action: “Choose one moment to be intentionally kind today. Micro is enough.”

### Appendix B: counselor fidelity log template

□ Student opened ≥4 nudges this week

□ Student submitted ≥1 reflective note this week

□ Student described ≥1 behavior aligned with weekly objective

Optional one-sentence remark: ____________________________.

### Appendix C: example micro-coaching dialogue (3–5 turns)

AI: “What small moment today challenged you most?”

Student: “During break they ignored me.”

AI: “What choice did you make in that moment?”

Student: “I walked away.”

AI: “Was that choice aligned with how you want to show up socially?”
